#### Sample size

The majority of quality indicators are categorical in nature (i.e., proportion of children who die in preferred location, proportion of children/parent who report symptoms in the severe range); therefore, sample size for this component of the project was calculated based on categorical analytic techniques. Specifically, sample size for standard Chi-square analysis was conducted and increased by a factor equivalent to the assumed design effect due to the clustering within regions. Given the timeline for the project and the number of children that die from cancer across Canada in a given year (~200), we will only be able to collect data on 100 deceased children in the 6 months following project implementation. However, retrospective health record reviews and surveys can be completed for a larger number of children at baseline. A prior study examining the effect of unit level interventions across 16 pediatric units across Canada, demonstrated moderate intra-class correlations (ICCs) for knowledge outcomes, but negligible ICCs for process and clinical outcomes [35]; therefore, a small ICC of 0.01 was used to adjust the sample size estimate to account for clustering within sites. We will complete a minimum of 200 health record reviews/surveys at baseline and 100 in the post-implementation period across all 16 sites to detect a 15 % difference in outcomes with 80 % power.

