#### Data analysis

Categorical data (e.g., location of care/death) and continuous data (e.g., parent reports of care quality scores) and will be summarized and descriptively reported using frequencies and proportions or means and standard deviations, respectively. To identify differences in the quality indicators between baseline and following implementation, marginal regression models (i.e. Generalized Estimating Equation models) will be used to model the outcome on time point (i.e. pre- versus post-test) and account for clustering of outcomes and practices of care within regions. All analyses will be conducted using SAS v9.3. A *p*-value of 0.05 or less will be used to indicate statistical significance.

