Our study is powered to detect changes in care quality. However, even if no changes are seen in the course of our study, measurement of the quality of palliative care for children with cancer on a national level is an important aspect of our study and will be a significant contribution to the field of pediatric oncology and palliative care. This wealth of data can be used as the basis for future research and targeted interventions to address specific issues nationally or locally. Ultimately our goal is to enhance the care of all children who live with life-threatening illnesses; we believe this study will be a significant step forward in achieving that goal.

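### The 80 % power stated for a 15-point change is too general: with 200 and 100 records it holds near the ends of the scale, but mid-range indicators have about 66-70 %

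*Protocol article*

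**What the plan says.** The sample size section under Stream 3 of the protocol article explains that most quality indicators are categorical and that the calculation was therefore built on categorical methods: "sample size for standard Chi-square analysis was conducted and increased by a factor equivalent to the assumed design effect due to the clustering within regions". For clustering, "a small ICC of 0.01 was used to adjust the sample size estimate to account for clustering within sites". The post-test number is set by the number of deaths: "we will only be able to collect data on 100 deceased children in the 6 months following project implementation". The section concludes: "We will complete a minimum of 200 health record reviews/surveys at baseline and 100 in the post-implementation period across all 16 sites", in order "to detect a 15 % difference in outcomes with 80 % power".

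It gives no baseline proportion and does not limit the 80 % to particular indicators or to one direction of change. Its two example indicators are death in the preferred location, where improvement is an increase, and symptoms in the severe range, where improvement is a decrease. The data analysis section adds "A *p*-value of 0.05 or less will be used to indicate statistical significance". The Discussion then states: "Our study is powered to detect changes in care quality".

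**The concern.** For a fixed absolute difference, the power of a two-proportion test depends on where the proportions lie. It is lowest when they straddle 50 % and rises towards 0 or 1. One figure of 80 % for 15 points therefore cannot describe a whole set of indicators unless it holds in the worst case. With 200 and 100 records it does not.

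What is at stake is how the care-quality results are read. The Discussion says that the study is powered and, in the next sentence, takes up the case where no change is seen. For a mid-range indicator, a true 15-point change would be missed about 30-34 % of the time, against the 20 % that the plan implies.

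**Working it through.** **Inputs.** From the sample size section: n1 = 200 before, n2 = 100 after, 16 sites, intra-class correlation (ICC) 0.01, a chi-square test, a 15 % difference and 80 % power. From the data analysis section: significance level 0.05.

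**Assumptions.** The test is two-sided, as a chi-square test is by nature. The 15 % is read as percentage points. The baseline proportion is not given, so the whole feasible range was scanned.

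**Formula.** Let d = |p2 − p1| and let p̄ = (n1·p1 + n2·p2)/(n1 + n2). Then

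- s0 = √[p̄(1 − p̄)(1/n1 + 1/n2)]
- s1 = √[p1(1 − p1)/n1 + p2(1 − p2)/n2]
- power ≈ Φ[(d − 1.96·s0)/s1]

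**Design effect**, 1 + (m − 1) × 0.01, with m the mean number of records per site:

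- before: m = 200/16 = 12.5, giving 1.115
- after: m = 100/16 = 6.25, giving 1.0525
- both periods pooled: m = 300/16 = 18.75, giving 1.1775

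Dividing each n by its design effect gives effective sizes of 179.4 and 95.0 (per period), or 169.9 and 84.9 (pooled).

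**Reproducing the plan's figure.** For 15 to 30 % at a 2:1 ratio, 80 % power needs 175 baseline records. Multiplied by 1.115 this is about 196, and by 1.1775 about 207, so the stated 200 lies between. For 70 to 85 % the need is 186, or about 208 to 220. The plan's figure is thus a plausible result for an indicator of this kind.

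**A mid-range indicator, 50 to 65 %.** With no design effect, p̄ = 0.55, s0 = 0.0609 and s1 = 0.0594. Then (0.15 − 1.96 × 0.0609)/0.0594 ≈ 0.515, so power = Φ(0.515) = 70 %. With the per-period sizes, s0 = 0.0631 and s1 = 0.0615. The argument becomes 0.428 and power 67 %.

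**Power (%) for a 15-point change**

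| Before → after | No design effect | Per period | Pooled |
|---|---|---|---|
| 15 → 30 | 85 | 82 | 79 |
| 20 → 35 | 80 | 77 | 73 |
| 35 → 50 | 70 | 67 | 63 |
| 40 → 55 | 69 | 66 | 62 |
| 45 → 60 | 69 | 66 | 62 |
| 50 → 65 | 70 | 67 | 62 |
| 60 → 75 | 74 | 71 | 67 |
| 70 → 85 | 83 | 80 | 76 |
| 25 → 10 | 90 | 87 | 84 |
| 30 → 15 | 83 | 80 | 76 |
| 75 → 60 | 76 | 73 | 69 |

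**Baselines at which 80 % is reached for 15 points** (scan in steps of one point)

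| Direction | No design effect | Per period |
|---|---|---|
| Increase | up to 19 %, or from 68 % | up to 16 %, or from 70 % |
| Decrease | up to 32 %, or from 81 % | up to 30 %, or from 84 % |

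Direction matters: 25 to 10 % is well powered, while 75 to 60 % is not.

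**Detectable change from a 50 % baseline with 80 % power:** 16.9 points with no design effect, 17.5 per period and 18.3 pooled.

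**Records needed for 50 to 65 % at 2:1, before clustering:** 256 + 128.

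**The case against.** The strongest reply is that the 80 % is not shown to be wrong. It reproduces for an ordinary input such as 15 to 30 %, and a condensed article may leave the planning baseline to the full protocol. That stands, and it rules out a stronger reading that a reader might infer, namely that the sample size was miscalculated. The documents do not support that reading. It does not rescue the wording, though. Whatever baseline was used, one figure is offered for the indicators as a class, and no single baseline can support that.

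A second reply is that the same 16 sites supply both periods, so part of the site effect cancels in the pre-post contrast and the real inflation may be near 1. This also stands. It makes the pooled design effect of 1.18, with its 62 % power, a pessimistic bound. Mid-range power with no inflation at all is still only 69-70 %.

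Other readings of the inputs do not recover 80 % under the stated method. A one-sided 5 % test with no clustering would give about 79-80 % in the mid-range, but that conflicts with the stated chi-square test and the stated inflation. A relative 15 % change gives far less power, about 20-23 % from a 50 % baseline. The numbers are called minimums, but the section itself says that only about 100 post-test deaths can be reached.

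Finally, a reader might infer that the plan will treat a null result as proof of no change. The article does not say so: its Discussion allows that longer follow-up may show more, and it values the national measurement in its own right.

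**Conclusion.** The power statement is overgeneralised. It is roughly right for indicators whose pre and post proportions lie towards 0 or 1, and too favourable for the rest. When both proportions fall between about 35 % and 65 %, the shortfall from 80 % is about 10-11 points of power with no clustering and 13-14 points with per-period design effects. On a 15-point increase, the stated power is missed for baselines between about 20 % and 67 % even with no clustering.

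This rests on a two-sided 5 % test, an absolute difference, exactly 200 and 100 records, equal numbers per site and the plan's own ICC. How many of the study's indicators are mid-range cannot be told from the article.

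**What to change.** Keep 200 and 100 and restate what they deliver, by baseline and direction. For example:

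> With 200 baseline and 100 post-test records (two-sided 5 %; no design effect / per-period design effect at ICC 0.01), power is at least 80 % for a 15-point increase from baselines up to about 19/16 % or from about 68/70 %, and for a 15-point decrease from baselines up to about 32/30 % or from about 81/84 %. When both proportions lie between about 35 % and 65 %, power for 15 points is about 69-70 % / 66-67 %. From a 50 % baseline, the change detectable with 80 % power is about 17/17.5 points.

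A note can add that a pooled design effect would take the last figure to about 18 points.

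Qualify the Discussion sentence on power in the same terms. If a particular baseline was used in planning, name it and tie the 80 % to indicators near it.

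The cost is wording only. Design, data collection and analysis stay as they are, and the stated power becomes less favourable for mid-range indicators.

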## Background

Despite significant improvements in treatment, childhood cancer remains a leading cause of non-accidental death in children beyond infancy [1]. Annually in Canada, about 10,000 children are living with cancer (both those receiving cancer treatments and long-term survivors) and approximately 210 will die from their disease [2]. Even when a child survives, from the moment of diagnosis the threat of death may be foremost in the mind of the parents, siblings, and ill child. The treatments aimed at achieving survival are generally intensive with a significant symptom burden that is often long-lasting and disruptive to the life of the child and family [3].

Palliative care for children focuses on alleviating the physical, social, psychological, and spiritual suffering experienced by children and families, while promoting quality of life, fostering family connections, and sustaining hope despite the possibility of death. It is a family-centered approach that includes shared decision-making and sensitivity to the family’s cultural and spiritual values, beliefs, and practices [4]. In relation to pediatric cancer, palliative care has historically been thought of as being relevant only once all treatments with curative intent have been discontinued, and is offered as an alternative rather than a concurrent treatment [5]. However, emerging data suggest that principles of palliative care can and should be incorporated from diagnosis and throughout the disease course, not only at the end of life, to ensure relief of suffering and good quality of life regardless of the disease outcome [6–10]. Consultation from specialist palliative care teams may be helpful for more complex situations [3].

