#### Sample and procedure: B) Health record reviews

Health record reviews will be conducted for all children with a cancer diagnosis who received treatment at one of the 16 pediatric oncology programs and died in the 12 months prior to the pre-test data collection (January 2014 to January 2015) and in the 6 months prior to the post-test data collection (June to November 2016).

Eligible deceased children will be identified through the Health Records Department. An on-site RA will review the health record and enter data directly into REDCap™. Data collection forms were developed based on previous health record reviews for children with cancer [9, 31, 32] and include information on diagnosis, age, location of death, involvement of a palliative care team, time spent in hospital during the last month of life, use of cancer directed treatments, and documentation of discussion of goals of care.

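### For health record reviews, the stated minimum of 200 and 100 is the whole number of deaths expected in the review windows, so the windows do not assure it

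*Protocol article*

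**What the plan says.** The Sample size section starts from "the number of children that die from cancer across Canada in a given year (~200" and concludes that "we will only be able to collect data on 100 deceased children in the 6 months following project implementation". It adds that "retrospective health record reviews and surveys can be completed for a larger number of children at baseline". It then commits to a size: "We will complete a minimum of 200 health record reviews/surveys at baseline and 100 in the post-implementation period across all 16 sites". With an intra-class correlation of 0.01, that size is said to give 80 % power for a 15 % difference.

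The section on health record reviews defines who is counted: "Health record reviews will be conducted for all children with a cancer diagnosis who received treatment at one of the 16 pediatric oncology programs". At baseline these are children who "died in the 12 months prior to the pre-test data collection (January 2014 to January 2015", and at post-test those who died "in the 6 months prior to the post-test data collection (June to November 2016". The Background gives a slightly higher national figure: "approximately 210 will die from their disease". The Discussion then says, without qualification, that the study has the power to detect changes in care quality.

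**The concern.** Within one paragraph, 100 is both the most that can be collected after implementation and the least that will be collected. Record review is already a census of the eligible deaths in fixed windows, so a shortfall cannot be made up by sampling more within them. If the expected yield equals the promised minimum, ordinary year-to-year variation is enough to miss it, and any unavailable record makes that more likely. The power statement for the record-review indicators would then rest on a size that the windows do not assure, and the Discussion carries that power statement forward.

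**Working it through.** **Inputs from the article.** National deaths: about 200 a year (Sample size) or about 210 (Background). Record-review windows: 12 and 6 months. Stated size: 200 and 100. Sites: 16. ICC: 0.01. Difference: 15 %, read as percentage points. Significance level: 0.05.

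**Assumptions, not in the article.** Deaths follow a Poisson distribution. A fraction c of the expected deaths is captured as reviewed records. The test is two-sided. The baseline rate is not given, so two settings are shown.

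**1. Reproducing the counts.** Expected deaths = annual deaths × months / 12.
- At 200 a year: 200 × 12/12 = 200 and 200 × 6/12 = 100. Both stated minima are matched exactly, with no reserve.
- At 210 a year: 210 and 105, a reserve of 5 %.

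**2. Chance of reaching the minima.** P(N₁ ≥ 200) with mean c × annual deaths, P(N₂ ≥ 100) with mean c × annual deaths / 2, and their product for both.

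| Deaths a year | Capture c | Expected | P(≥ 200) | P(≥ 100) | Both |
|---|---|---|---|---|---|
| 200 | 100 % | 200 / 100 | 0.51 | 0.51 | 0.26 |
| 210 | 100 % | 210 / 105 | 0.76 | 0.70 | 0.53 |
| 200 | 95 % | 190 / 95 | 0.24 | 0.32 | 0.08 |
| 210 | 95 % | 199.5 / 99.75 | 0.50 | 0.50 | 0.25 |

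**3. What a shortfall does to power.** Two-proportion test with pooled variance under the null. Each period's count is divided by its design effect, 1 + (n/16 − 1) × 0.01.
- At 200/100: design effects 1 + 11.5 × 0.01 = 1.115 and 1 + 5.25 × 0.01 = 1.0525, so effective sizes are 179.4 and 95.0.
- At 180/90 (a 10 % shortfall, for illustration): design effects 1.1025 and 1.04625, so effective sizes are 163.3 and 86.0.

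| Rates compared | Power at 200/100 | Power at 180/90 |
|---|---|---|
| 15 % vs 30 % | 82 % | 79 % |
| 42.5 % vs 57.5 % | 66 % | 62 % |
| 35 % vs 50 % | 67 % | 63 % |

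The stated 80 % can therefore be reproduced at 200/100 when the lower rate is near 15 %. The shortfall itself costs about 3 to 5 points. The gap between 82 % and 66-67 % comes from the assumed rate and not from the windows.

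**4. Why the surveys are different.** The bereaved-parent windows are 2 years and 8 months, which hold 200 × 2 = 400 and 200 × 8/12 ≈ 133 deaths. Those counts exceed 200 and 100, so the equality in step 1 does not arise. The active-treatment surveys are not limited by deaths at all.

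**The case against.** The strongest reply is that this is a loose word and not a design fault. The article discloses the post-test limit, record review needs no consent or response, and all eligible deaths will be reviewed whatever the number is called. The national figure is rounded, and at 210 a year the chance of reaching both counts is about even. The eligible set is also not strictly a subset of the 200: the record-review section takes any deceased child with a cancer diagnosis treated at the programs, with no limit on cause of death or age stated there, so the yield could be higher as well as lower. All of this stands, and it limits the size of the point. It does not turn an expected total into a minimum.

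Three stronger readings are tempting, and the article does not support them.
- A reader might infer that the remark about a larger number at baseline contradicts the 12-month window. It does not: the contrast is with 100 post-test, and 200 is larger. The 2-year window belongs to the bereaved-parent survey, where parents are not approached for at least 6 months after the death.
- A reader might infer that capture will be about 90 % and that both minima are almost certain to be missed. The article gives no capture rate, so any such figure is an assumption.
- A reader might infer that the windows pull power from 80 % down to about 66 %. That drop follows from placing the unstated baseline rate near 50 %.

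**Conclusion.** The point holds for the health record reviews only. On the article's own deaths and windows, 200 and 100 are the expected yield of a complete census, and the same section describes 100 as all that can be collected post-test. Calling them a minimum, with power attached, is wrong as written. How likely both are to be met depends on the input: about one in four at 200 deaths a year, about even at 210, and lower with any net loss of records. These chances assume Poisson counts and an eligible population close to the national figure. The consequence for power is small, about 3 to 5 points for a 10 % shortfall, so this is a correction to a stated size and its power, and no threat to the design.

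**What to change.** In the Sample size section, separate the record reviews from the surveys. For record reviews, replace the minimum of 200 and 100 with all eligible deaths in the windows, expected to number about 200 and 100. State power over a plausible range of yields, and name the baseline rate assumed. With the design effect, that would read, for example, about 82 % at 200/100 and 79 % at 180/90 for 15 % vs 30 %, and about 66-67 % and 62-63 % for rates near 50 %. Qualify the Discussion's power claim for record reviews in the same terms. This costs only wording and changes no data collection, but the stated size and power become less favourable.

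Optionally, lengthen the record-review baseline window to 2 years. That gives about 400 expected baseline deaths (200 × 2) and so secures the baseline count, at the cost of about 200 more retrospective charts. It leaves the limiting post-test count at about 100, so the restated wording would still be needed.

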#### Data analysis

Categorical data (e.g., location of care/death) and continuous data (e.g., parent reports of care quality scores) and will be summarized and descriptively reported using frequencies and proportions or means and standard deviations, respectively. To identify differences in the quality indicators between baseline and following implementation, marginal regression models (i.e. Generalized Estimating Equation models) will be used to model the outcome on time point (i.e. pre- versus post-test) and account for clustering of outcomes and practices of care within regions. All analyses will be conducted using SAS v9.3. A *p*-value of 0.05 or less will be used to indicate statistical significance.

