Eligible children and parents will be approached during an inpatient stay or regular clinic visit by their primary nurse or other health professional actively involved in their care to see if they are interested in learning more about our study. If so, the Research Assistant (RA) will meet with the parent and child to provide further information about the study. Assent/consent will be obtained from eligible children and parents. If both parents are present, they will be asked to choose one parent to complete the survey. If the child is less than seven years old or if the child does not wish to complete a survey, the parent will still be asked to participate in the study. The RA will have hard copies of all assent/consent forms available, but the assent/consent forms will also appear in REDCap™ prior to any questions being asked. Submission of the survey signifies assent/consent. Children and parents who agree to take part will be given the option of completing the survey with the RA (i.e., the RA would access REDCap™, read the questions to the participant, and enter the responses), providing an email address where a link to the survey on REDCap™ can be sent, or taking a business card that has the survey link written on it so the participant can complete the survey on their own. Children/adolescents will be offered a certificate of completion for taking part in the study. Eligible children/parents will be approached only once during each data collection period to take part in the study; however, a child/parent who was approached during the pre-test period (Winter 2015) may be approached again during the post-test period (Fall 2016) if they still meet the eligibility criteria. Families who take part in both the pre- and post-testing period will not have their responses linked, as we are interested in cross-sectional data rather than longitudinal.

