Our study design and timelines will allow us to adequately measure the impact of the EPEC®-Pediatrics curriculum roll-out on self-assessed knowledge improvements of health professionals; knowledge transfer and dissemination outcomes; and practice change outcomes, as has been done in the past [20]. However, our study will be the first to examine the impact on a national level. We have chosen a pre- post-test design to evaluate our intervention in terms of its impact on quality of care. A recent systematic review indicated that a train-the-trainer model is effective in improving patient outcomes; however, the length of the intervention and timing of data collection varied widely across studies [22]. Therefore, there is little evidence available to determine an optimal length of the intervention or timing for outcome assessment that could be used to guide a stronger design, such as a cluster randomized controlled trial. It is possible that a longer intervention period and a longer follow-up period for post-test data collection may show greater improvements in patient outcomes. Additionally, though one of the strengths of EPEC®-Pediatrics is the breadth of knowledge covered in the curriculum and the flexibility that Trainers have in choosing which aspects of the curriculum to present to End-Users, this flexibility means that the roll-out may look very different across the participating sites. To address some of the limitations we will explore differences in how the curriculum has been rolled out in each site (e.g., number and type of education sessions, number of End-Users, type and success of QI projects) and whether these differences are associated with any differences in quality of palliative care across sites. This exploration may help to identify some core components of the curriculum that must be included as part of the intervention and may advance the science such that a stronger design could be used in future research to roll-out the curriculum to health professionals who care for children with life-threatening illnesses other than cancer.

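### The Stream 3 GEE names only time point, so a systematic shift in case mix or timing between the two unrandomised periods would be read as an effect of the roll-out

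*Protocol article*

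**What the plan says.** Protocol article, Stream 3, Data analysis: "marginal regression models (i.e. Generalized Estimating Equation models) will be used to model the outcome on time point (i.e. pre- versus post-test", and the model is to "account for clustering of outcomes and practices of care within regions". No patient covariate, site term or calendar term is named there or elsewhere in the article.

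The Discussion describes the design: "We have chosen a pre- post-test design to evaluate our intervention in terms of its impact on quality of care". There is no control group.

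The samples are described in the Stream 3 introduction and in parts A to C:

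- Active-treatment families may take part in both periods but "will not have their responses linked, as we are interested in cross-sectional data rather than longitudinal".
- Record reviews take baseline deaths from January 2014 to January 2015, and post-test deaths "in the 6 months prior to the post-test data collection (June to November 2016".
- Bereaved parents are drawn from a 2-year window of deaths at baseline and an 8-month window afterwards.
- The record-review forms "include information on diagnosis, age, location of death, involvement of a palliative care team, time spent in hospital during the last month of life".

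The Sample size section sets minimum totals of 200 at baseline and 100 post, across all 16 sites, to detect a 15 % difference with 80 % power at an ICC of 0.01.

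**The concern.** In an uncontrolled before-and-after comparison, the period coefficient absorbs anything that differs between the periods, not just the intervention. If the post-test sample has a different balance of diagnoses or ages, or comes from a different part of the year, and the indicator depends on those things, the difference appears in the coefficient as a change in care quality. It could create an apparent improvement or hide a real one.

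Allowing for clustering mainly corrects the standard error. It does not take a case-mix shift out of the estimate.

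The point concerns a model that the article states, not only detail left unsaid. For the record reviews, the two obvious adjusters are already on the form.

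**Working it through.** **1. Are the periods comparable by design?**

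| Source | Baseline | Post |
|---|---|---|
| Active-treatment surveys | January–April 2015 | September–November 2016 |
| Record reviews (deaths) | 12 months, January 2014 to January 2015 | 6 months, June–November 2016 |
| Bereaved parents (deaths) | July 2012 to July 2014, letters January 2015 | December 2015 to July 2016, letters January 2017 |

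No source uses the same season and window length in both periods. On the article's example dates, time from death to invitation is about 6 to 30 months at baseline and about 6 to 13 months afterwards.

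**2. The plan's own yardstick.** The target is 15 points (read as absolute) with 200 and 100. The 80 % power cannot be reproduced uniquely, because no baseline proportion is given. With design effect 1 + (12.5 − 1) × 0.01 = 1.115 (12.5 = 200/16) and a two-sided 5 % test, power is 65 % for 0.50 against 0.65 and 81 % for 0.15 against 0.30. This does not decide the present point; the 15 points serve only as a scale.

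**3. Bias from a case-mix shift.** For a binary factor, and with no true effect:

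bias in the contrast = (shift in the factor's prevalence) × (risk difference carried by the factor)

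Neither input is in the documents, so both are assumed and shown as a range (in points):

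| Risk difference | Shift 5 | Shift 10 | Shift 15 | Shift 20 |
|---|---|---|---|---|
| 10 | 0.5 | 1.0 | 1.5 | 2.0 |
| 20 | 1.0 | 2.0 | 3.0 | 4.0 |
| 30 | 1.5 | 3.0 | 4.5 | 6.0 |
| 40 | 2.0 | 4.0 | 6.0 | 8.0 |

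For example, 0.10 × 0.30 = 0.03, or 3 points; 3/15 = 20 % of the target.

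**4. Simulation check.** 16 sites, 200 pre and 100 post, no true effect, site SD 0.05, risk difference 0.30, 600 runs per scenario:

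| Prevalence shift | Time-only GEE: estimate, rejection | GEE plus the factor: estimate, rejection |
|---|---|---|
| 10 points | +0.030, 12 % | 0.000, 8 % |
| 20 points | +0.056, 18 % | −0.004, 7 % |

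The time-only results agree with step 3, and the covariate removes the bias. The 7–8 % left over is the usual excess with few clusters.

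**5. Site mix.** An ICC of 0.01 at a proportion of 0.5 implies a between-site SD of √(0.01 × 0.25) = 0.05. With post-period site weights tilted by 30 % toward better sites, the time-only estimate moved by about +0.01 at that SD. At an assumed SD of 0.15 it moved by +0.035 under an independence working correlation and +0.013 under exchangeable. Site terms (fitted together with the covariate) brought it to about zero.

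**The case against.** - **The covariate list may sit in a fuller document.** The article does not say that the model is unadjusted. A reader might infer that adjustment has been ruled out; the text does not go that far. It does state the regressor, though, and nothing else in it supplies adjustment: the Discussion promises only to explore whether roll-out differences between sites go with differences in care quality. Improving a stated model is a fair point.
- **Chance imbalance is not bias.** A reader might calculate that a diagnosis group with an assumed 40 % share differs between periods with SE √(0.24 × (1/200 + 1/100)) = 0.060, a 95 % range of about ±12 points, and count 0.118 × 30 = 3.5 points as bias. That is sampling variation, and the unadjusted standard error already contains it. Only a systematic shift biases the estimate, and the documents give no evidence of its size.
- **A large site effect conflicts with the plan's ICC.** A reader might add that a site rising from 20 % to 30 % of the sample and lying 30 points from the rest moves the contrast by 3 points, making 6.5/15 = 43 % of the target. A 30-point deviation is 0.30/0.05 = 6 SD on the plan's own ICC. The record reviews also take all deaths in each window, so site shares change only if the sites' deaths do. This larger figure is not supported.
- **The samples are not wholly different children.** That holds for the deceased-child sources only; active-treatment families may appear twice, unlinked.
- **Age and diagnosis are listed only for the record form.** The survey descriptions do not itemise them, so one adjusted model for all three sources cannot be assumed feasible.
- **Site fixed effects are heavy as a main model.** Fifteen site terms with 16 clusters and about 100/16 ≈ 6 post records per site would strain robust inference and could produce separation.

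All of these stand as limits on the size and the remedy. None answers the core: a systematic shift passes straight into a time-only coefficient.

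**Conclusion.** The point holds in a limited form. The mean model as stated has time point only, while the two periods are unrandomised samples from windows of different length and season. A systematic shift in case mix or timing would therefore be read as an effect of the roll-out.

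Its actual size is unknown. Over the assumed range the bias runs from 0.5 to 8 points; the 10-point, 30-point example gives 3 points against the 15-point target. Case mix and timing carry the argument. At the plan's ICC, site mix adds about 1 point in the scenario tried.

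The documents do not show that a shift will occur, so they do not support concluding that the planned comparison is biased by a known or large amount.

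**What to change.** **Main model, record reviews.** Prespecify the GEE as period + age group + diagnosis group, with clustering by site, and report the unadjusted estimate beside it.

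**Surveys.** Use the same adjustment wherever age and diagnosis are recorded.

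**Sensitivity analyses.**

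- A within-site contrast using site terms, with small sites pooled.
- A season check for the record reviews, restricting baseline deaths to June–November 2014. A term for the calendar half-year of death should not be used in its place: if it is year-specific, it is aliased with period.

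**Cost.** Some wording, slightly more analysis and a few extra parameters. The record reviews need no new data items. The season check is less precise: if it leaves about 100 of 200 baseline deaths (assuming deaths spread evenly over the year), the SE at a proportion of 0.5, before any design effect, rises from √(0.25 × (1/200 + 1/100)) = 0.061 to √(0.25 × (1/100 + 1/100)) = 0.071.

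**What this does not cure.** Adjustment cannot remove secular trend. The active-treatment survey seasons do not overlap, so season there cannot be separated from period. Age and diagnosis terms do not address the longer time since death among baseline bereaved parents. The report should state these limits.
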